## Abstract

**Background:**

Besides motor impairments, up to 90% of the children and adolescents with unilateral cerebral palsy (uCP) present with somatosensory impairments in the upper limb. As somatosensory information is of utmost importance for coordinated movements and motor learning, somatosensory impairments can further compromise the effective use of the impaired upper limb in daily life activities. Yet, intervention approaches specifically designated to target these somatosensory impairments are insufficiently investigated in children and adolescents with uCP. Therefore, the aim of this randomized controlled trial (RCT) is to compare the effectiveness of somatosensory discrimination therapy and dose-matched motor therapy to improve sensorimotor upper limb function in children and adolescents with uCP, who experience somatosensory impairments in the upper limb. We will further explore potential behavioral and neurological predictors of therapy response.

**Methods:**

A parallel group, evaluator-blinded, phase-II, single-center RCT will be conducted for which 50 children and adolescents with uCP, aged 7 to 15 years, will be recruited. Participants will be randomized to receive 3 weekly sessions of 45 minutes of either somatosensory discrimination therapy or upper limb motor therapy for a period of 8 weeks. Stratification will be performed based on age, manual ability, and severity of tactile impairment at baseline. Sensorimotor upper limb function will be evaluated at baseline, immediately after the intervention and after 6 months follow-up. The primary outcome measure will be bimanual performance as measured with the Assisting Hand Assessment. Secondary outcomes include a comprehensive test battery to objectify somatosensory function and measures of bimanual coordination, unimanual motor function, and goal attainment. Brain imaging will be performed at baseline to investigate structural brain lesion characteristics and structural connectivity of the white matter tracts.

**Discussion:**

This protocol describes the design of an RCT comparing the effectiveness of somatosensory discrimination therapy and dose-matched motor therapy to improve sensorimotor upper limb function in children and adolescents with uCP. The results of this study may aid in the selection of the most effective upper limb therapy, specifically for children and adolescents with tactile impairments.

**Trial registration:**

ClinicalTrials.gov (NCT06006065). Registered on August 8, 2023.

**Supplementary Information:**

The online version contains supplementary material available at 10.1186/s13063-024-07967-4.

## Administrative information

Note: the numbers in curly brackets in this protocol refer to SPIRIT checklist item numbers. The order of the items has been modified to group similar items (see http://www.equator-network.org/reporting-guidelines/spirit-2013-statement-defining-standard-protocol-items-for-clinical-trials/).

**Table Taba:** 

Title {1}	Does somatosensory discrimination therapy alter sensorimotor upper limb function differently compared to motor therapy in children and adolescents with unilateral cerebral palsy: study protocol for a randomized controlled trial
Trial registration {2a and 2b}.	Primary registry and trial identifying number: ClinicalTrials.gov, NCT06006065 Date of registration in primary register: August 8, 2023 Secondary identifying numbers: G0C4919N, S67467 Source(s) of monetary or material support: The Flemish Research Foundation provides financial support for this study (FWO project, G0C4919N; FWO-fellowship [name], 11PP224N). Primary sponsor: KU Leuven Contact for public queries: [name]; [name]; [contact] ; [name] Contact for scientific queries: PI: [name], Scientific contact delegate: [name]; [name]; [contact] ; [name] Public title: The effectiveness of an intensive therapy program for the upper limb in children and adolescents with unilateral cerebral palsy Scientific title: The effectiveness of an intensive upper limb therapy program focused on somatosensation in children and adolescents with unilateral cerebral palsy Countries of recruitment: Belgium Health condition(s) or problem(s) studied: Unilateral cerebral palsy Intervention(s): Intervention: Upper limb somatosensory discrimination therapy (18 hours over 8 weeks); Active comparator: Upper limb motor therapy (18 hours over 8 weeks) Key inclusion and exclusion criteria: Ages eligible for study: 7 to 15 years; Sexes eligible for study: both; Accepts healthy volunteers: no; Inclusion criteria: (1) Diagnosis of predominantly spastic unilateral cerebral palsy; (2) Aged 7 to 15 years old at the time of baseline assessment; (3) Sufficient cooperation to comprehend and complete the test and therapy procedures; (4) Minimal ability to actively grasp and hold an object with the more impaired hand (Modified House Functional Classification System ≥ 4); and (5) Having a confirmed impairment in tactile registration and/or tactile perception, as objectified using a clinical assessment battery described under the section ‘eligibility screening’; Exclusion criteria: (1) Botulinum toxin-A injections six months prior to baseline testing; (2) A history of upper limb surgery one year prior to baseline testing; and (3) Inability to communicate in Dutch Study type: Type of study: Interventional; Allocation: randomized; Interventional model: parallel assignment; Masking: single blind (assessor); Primary purpose: clinical intervention; Phase: II Date of first enrollment: August 2023 (actual) Target sample size: 50 (anticipated) Recruitment status: Started on August 8, 2023 Primary outcome(s): Outcome name: Bimanual performance; Method of measurement: Assisting Hand Assessment (AHA); Timepoint: 6 months after the therapy has ended (follow-up) Key secondary outcomes: • Outcome name: Bimanual performance; Method of measurement: Assisting Hand Assessment (AHA); Timepoint: immediately after therapy has ended (post-intervention) • Outcome name: Bimanual performance; Method of measurement: Children’s Hand-use Experience Questionnaire (CHEQ); Timepoint: immediately after therapy has ended (post-intervention) and 6 months after the therapy has ended (follow-up) • Outcome name: Bimanual coordination; Method of measurement: Box opening task; Timepoint: immediately after therapy has ended (post-intervention) and 6 months after the therapy has ended (follow-up) • Outcome name: Bimanual coordination; Method of measurement: Kinarm Exoskeleton (‘Ball-on-bar task’); Timepoint: immediately after therapy has ended (post-intervention) and 6 months after the therapy has ended (follow-up) • Outcome name: Tactile registration; Method of measurement: Semmes–Weinstein Monofilaments; Timepoint: immediately after therapy has ended (post-intervention) and 6 months after the therapy has ended (follow-up) • Outcome name: Tactile perception; Method of measurement: Stereognosis, Aesthesiometer, Tactile Discrimination Test; Timepoint: immediately after therapy has ended (post-intervention) and 6 months after the therapy has ended (follow-up) • Outcome name: Proprioception; Method of measurement: Kinarm Exoskeleton (‘Contralateral position matching task’, ‘Perceptual boundary task’, ‘Indicating location task’), ETH MIKE (‘Passive position sense task’), Clinical assessment of movement sense; Timepoint: immediately after therapy has ended (post-intervention) and 6 months after the therapy has ended (follow-up) • Outcome name: Unimanual motor function; Method of measurement: Tyneside Pegboard Test; Timepoint: immediately after therapy has ended (post-intervention) and 6 months after the therapy has ended (follow-up) • Outcome name: Self-perceived occupational performance and goal attainment; Method of measurement: Canadian Occupational Performance Measure (COPM), Goal Attainment Scaling (GAS); Timepoint: immediately after therapy has ended (post-intervention) and 6 months after the therapy has ended (follow-up)

## Introduction

### Background and rationale {6a}

When performing activities of daily living, such as filling a drinking cup or jumping rope, we continuously rely on the process of sensorimotor integration for successful task performance [1]. Sensorimotor integration has been described as the ability to integrate sensory information from various modalities, while simultaneously transforming these inputs into motor actions [2]. More specifically, our somatosensory system provides relevant information on the characteristics of objects, such as their form, weight, and size. Also information regarding the position and movements of our body parts in space is provided, which is critical for a smooth interaction with these objects [1, 2]. As such, somatosensory impairments can significantly disturb the process of sensorimotor integration, leading to difficulties when performing goal-directed activities and exploring the environment [1, 3–5].

This is often the case for children and adolescents with neurological disorders, such as cerebral palsy (CP). CP is the most common physical disability in childhood, arising from an injury or malformation of the developing brain [6, 7]. Unilateral cerebral palsy (uCP) is a prevalent subtype, accounting for up to 44% of the cases [8]. Children and adolescents with uCP present with motor and somatosensory impairments predominantly at one side of the body, which are often more pronounced in the upper compared to the lower limb [9]. Although CP has been primarily defined as a motor disorder, previous research has shown that up to 90% of the children and adolescents with uCP also present with impairments in one or more modalities of somatosensation [10–12].

Somatosensation comprises all aspects of touch and proprioception that contribute to a person’s awareness of his or her body parts in space and the direct interface of these body parts with objects and the environment in the absence of vision [13]. Somatosensory impairments can occur across different modalities of somatosensation, including tactile registration, tactile perception, and proprioception. Tactile registration comprises the awareness of an external stimulus, while tactile perception also includes its interpretation [14]. Proprioception, on the other hand, refers to the ability to perceive limb positions and movements [15]. For example when filling a drinking cup, tactile registration and perception are needed to provide information on the cup’s texture and weight which is needed to adequately tune grip force [16], while proprioception ensures that the position of both hands relative to each other is properly maintained as the cup is filled and its weight increases [17].

As such, accurate somatosensory information is crucial for motor control and motor learning [1, 18, 19]. In children and adolescents with uCP, the presence of somatosensory impairments has shown to be related to worse motor performance, diminished fine motor skills, and reduced use of the impaired upper limb during bimanual activities [10, 20–25]. As a result, developmental experiences will be restricted, limiting somatosensory input and motor development even more [6]. This vicious circle emphasizes the importance of addressing these somatosensory impairments during rehabilitation [26, 27], to improve the use of the more impaired upper limb during bimanual daily life activities potentially further and as such stimulate developmental experiences, functional independence, and quality of life.

Up until now, improvements in somatosensory function are mostly considered as a potential by-product of motor training [28]. Some studies have indeed shown that after constraint-induced movement therapy [29] and bimanual motor therapy [30–32], significant improvements in somatosensory function can be detected, although the results are varying depending on the type of participants, specific intervention performed, and the outcome measures used. Furthermore, based on the training principle of specificity, it can be expected that interventions designated to specifically address these somatosensory impairments might have a superior effect. However, the effectiveness of such intervention approaches has scarcely been investigated in children and adolescents with uCP [28, 33, 34], despite growing evidence in adult stroke patients.

Given the lack of strong evidence regarding somatosensory therapy approaches specifically for children with uCP, Auld and colleagues identified therapy approaches used in adult stroke patients that may also be beneficial for children and adolescents [35]. Transfer enhanced somatosensory discrimination therapy, also known as Sense© therapy, was one of the recommended approaches [36]. Sense© therapy is a highly structured therapy approach based on the principles of perceptual learning and learning-dependent neuroplasticity. It consists of repeated and graded practice discriminating differences in a variety of stimuli across somatosensory modalities, and the practice of daily life activities with targeted attention for somatosensory aspects necessary for successful task completion [37]. The effectiveness of this therapy to improve somatosensory impairments and functional upper limb use in adult stroke patients has been investigated earlier [35, 36, 38–40]. In 2017, McLean and colleagues modified the original concept of this therapy to accommodate the specific needs of children and adolescents, resulting in the Sense for Kids therapy [41]. Based on a feasibility study in children and adolescents with uCP [41], this therapy might improve somatosensory function, goal attainment, and motor performance. Furthermore, Sense for Kids therapy has shown to be feasible and engaging [42]. The full potential and the long-term effects of this therapy in comparison to upper limb motor therapy, however, still need to be investigated in a randomized controlled trial (RCT).

Despite having the same diagnosis, large inter-individual variability with regard to sensorimotor upper limb function and therapy response after motor therapy is seen in children and adolescents with uCP [43–48]. This variability has led researchers to investigate potential predictors of therapy response in order to determine which children and adolescents may benefit most from which type of upper limb therapy. Previous studies have already investigated potential neurological and behavioral predictors, however, sample sizes were often limited and only motor-based interventions were considered [32, 45, 46, 49–51]. Which predictors can be identified for somatosensory discrimination therapy remains to be investigated.

In summary, somatosensory function has shown to be crucial for upper limb motor function [1]. However, evidence underpinning the effectiveness of therapy approaches that specifically target somatosensory impairments is still scarce. Based on an earlier study, Sense for Kids has been proposed as a feasible and potentially effective therapy approach to improve bimanual performance and somatosensory function in children and adolescents with uCP. Yet, the effectiveness of this therapy to improve sensorimotor upper limb function when compared to upper limb motor therapy, its long-term effects, and potential predictors of therapy response still remain to be explored in an RCT.

## Objectives {7}

Therefore, this study protocol describes the design of an RCT comparing the efficacy of Sense for Kids therapy and dose-matched motor therapy to improve sensorimotor upper limb function in children and adolescents with uCP, who present with tactile impairments in the more impaired upper limb. The primary objective is to investigate if somatosensory discrimination therapy results in better bimanual performance at 6 months follow-up, compared to upper limb motor therapy. Secondly, we will investigate if somatosensory discrimination therapy is superior to improve somatosensory impairments. Lastly, we will explore the potential role of behavioral and neurological predictors of therapy response. The results of this study may aid in the selection of the most effective therapy intervention, specifically for children and adolescents with uCP who present with tactile impairments in the upper limb.

We hypothesize that somatosensory discrimination therapy will result in equal improvements in bimanual performance compared to upper limb motor therapy, immediately after the intervention period. However, we expect further improvements in bimanual performance during the follow-up period for participants who received somatosensory discrimination therapy because of the improved upper limb use in daily life, but not after upper limb motor therapy. We further hypothesize larger improvements in proprioceptive function and tactile perception, both immediately after the intervention and at follow-up, in participants who received somatosensory discrimination therapy. By considering the content and organization of the somatosensory discrimination therapy, we expect a higher therapy response for children and adolescents with worse somatosensory function and better attentional functioning at baseline. Lastly, we hypothesize that the occurrence of thalamic lesions is an important predictor of therapy response, because of the crucial role this brain structure has in the processing of somatosensory information that is transmitted from the periphery to the cortex [52].

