### Sample size {14}

The sample size calculation is based on the primary objective, which is defined as the retention of therapy effects on the primary outcome measure being bimanual performance measured with the Assisting Hand Assessment (AHA) at 6 months follow-up. The smallest detectable difference has been reported to be 5 AHA units [62]. Based on a previous intervention study in children with uCP [46], a standard deviation of 5.5 AHA units for improvements after intensive upper limb therapy was calculated by taking the average of the standard deviations between baseline and post-intervention and baseline and follow-up of both intensive therapy groups. The sample size estimate was calculated with G*Power for the following statistical test “Means: Difference between two independent means (two groups)” [63, 64]. With an estimated difference of 5 AHA units in the mean improvement between the intervention and control group and a standard deviation of 5.5 AHA units for both groups, an effect size of 0.9 was calculated. Based on an effect size of 0.9, an alpha level of 0.05 and a statistical power of 0.80, a sample size of at least 21 participants is needed in each group to detect a difference equal to or larger than the smallest detectable difference of 5 AHA units between groups. This number will be increased to 25 per group to account for inevitable dropouts and to maximize the study sample for prediction purposes.

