## Statistical methods

### Statistical methods for primary and secondary outcomes {20a}

All observations will be summarized as mean and standard deviation or median and interquartile range, according to the nature of the data. Baseline comparability between groups will be visually checked based on descriptive statistics. As the participants will be randomized to the intervention or control group, statistical testing of baseline differences will not be performed [108]. To study the time effects of the intervention and to allow for comparison between both groups, linear or generalized mixed models will be applied for the primary and secondary outcome measures. By using random effects, such models correct for the relation among repeated observations within subjects. An additional benefit of these models is that they provide a valid inference for missing values that are (completely) at random [109]. In case the data of an outcome measure is not normally distributed based on the Shapiro–Wilk test and/or visual inspection of the data distribution, transformations will be applied. The main endpoint will be to investigate if there is a difference in evolution of the AHA score over time between both groups. As such, interactions between therapy and time will be analyzed to test for differences in improvements over time between both groups (time*group interaction effect). When a significant interaction is identified, time trends will be tested in both therapy groups separately (time-effect). When the interaction is not significant, the main effect of time will be explored. Effect sizes for the full models will be further calculated using the Cohen’s partial η^2^ formula [partial η^2^ = (F × df_between_)/((F × df_between_) + df_within_)] [110]. Significant time trends will be further investigated with pairwise post hoc tests to compare individual time points (*T*_0_–*T*_1_, *T*_1_–*T*_2_, *T*_0_–*T*_2_). For the model of the primary outcome measure, the post hoc analysis will be Bonferroni corrected and the pairwise post hoc test for *T*_0_–*T*_2_ will be the primary outcome. For the models of secondary outcome measures, a false discovery rate with an adjusted *p*-value of 0.05 will be implemented. Effect sizes of these comparisons will be calculated using Cohen’s d formula [111]. For the second research objective, we will investigate predictive factors of therapy response. Both behavioral and neurological characteristics, i.e., somatosensory function at baseline, attentional functioning, and thalamic volume, will be included as covariates in the model for the primary outcome measure. All statistical analyses will be performed in SPSS Statistics for Windows. Level of significance will be set at 0.05, two-sided. When needed, adapted statistical techniques will be applied in close collaboration with Leuven Biostatistics and statistical Bioinformatics Centre (L-BioStat).

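### The hypothesis of equal AHA gains immediately after therapy is not answered by the planned tests, and a non-significant difference can leave a gap above 5 units open

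*Protocol article*

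**What the plan says.** Objectives {7} sets the primary objective as a superiority question at six months (T2): "if somatosensory discrimination therapy results in better bimanual performance at 6 months follow-up, compared to upper limb motor therapy". The same section then states what is expected at T1, namely that "somatosensory discrimination therapy will result in equal improvements in bimanual performance compared to upper limb motor therapy, immediately after the intervention period", with further gains during follow-up in the somatosensory arm only. The AHA at T1 is listed as a secondary outcome in the registration table and in Table 1.

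Sample size {14} rests on a difference. The anchor is "The smallest detectable difference has been reported to be 5 AHA units". The assumptions are "With an estimated difference of 5 AHA units in the mean improvement between the intervention and control group", "a standard deviation of 5.5 AHA units for both groups" and "an alpha level of 0.05 and a statistical power of 0.80", giving 21 per group, raised to 25.

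Statistical methods {20a} fits a mixed model and tests the time-by-group interaction, with "Level of significance will be set at 0.05, two-sided". A significant interaction leads to tests of the time trend in each arm separately. Otherwise, "When the interaction is not significant, the main effect of time will be explored". Pairwise comparisons of time points follow significant time trends. The section names no between-arm contrast at T1 and gives no rule for judging whether the T1 gains are equal.

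**The concern.** Equality and difference need different evidence. Failing to find a difference does not show that two arms are alike, least of all with 21 to 25 children each. Both branches of {20a} miss the T1 question:

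- **Interaction not significant.** This does not show equal gains at T1, and the next step is a time effect shared by both arms.
- **Interaction significant.** If the hypothesised pattern is true (equal at T1, apart at T2), T2 may drive the result, which then says nothing about T1. The prescribed follow-up is within each arm, and setting two within-arm results side by side is not an estimate of the difference between them.

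At stake is the explanation that somatosensory therapy matches motor therapy at first and overtakes it during follow-up. The first half of that account could be reported without the trial having examined it.

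**Working it through.** **Inputs, all from Sample size {14} and Statistical methods {20a}:** SD of change 5.5 AHA units per arm; difference to detect 5 units; two-sided alpha 0.05; power 0.80; 21 evaluable and 25 randomised per arm. The SD can be used at T1 because {14} averages SDs of change to post-intervention and to follow-up.

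**The plan's own figure.** d = 5/5.5 = 0.909, stated as 0.9. For a two-sample t-test (noncentral t, two-sided 0.05, d = 0.9), power is 0.792 with 20 per arm and 0.812 with 21. The stated 21 per group is reproduced.

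**Precision at T1.** SE = 5.5 × √(2/n), and the 95% half-width is t(0.975, 2n − 2) × SE. A result that just misses significance has an observed gap equal to the half-width, so its far limit is twice that.

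| | n = 21 | n = 25 |
|---|---|---|
| SE | 1.70 | 1.56 |
| 95% half-width | 3.43 | 3.13 |
| Far 95% limit, just non-significant | 6.86 | 6.26 |
| Observed gap above which the CI passes 5 (5 − half-width) | 1.57 | 1.87 |

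An observed gap of zero gives a CI of ±3.43 or ±3.13, which excludes 5. So non-significance leaves a gap above 5 open for some observed results and not for others.

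**How often this matters** (simulation, 400,000 draws, SD estimated in each draw; n = 21, then n = 25):
- True gap 3 units: non-significant in 59% and 53% of trials.
- True gap 5 units: non-significant in 18% and 12%.
- Arms truly equal: among non-significant results, 33% and 19% have a CI reaching beyond 5.

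**Whether equality could be tested at this size.** The protocol gives no margin, so ±5 is an assumption and smaller values show the range. The rule is that the 90% CI lies inside the margin (two one-sided tests at 0.05). The 90% half-widths are 2.86 and 2.61, so a ±5 margin is met for observed gaps up to about 5 − 2.86 = 2.14 or 5 − 2.61 = 2.39.

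| Margin | Power if truly equal, n = 25 | n per arm for 80% power |
|---|---|---|
| 5 | 87% (79% at n = 21) | 22 |
| 4 | 63% | 34 |
| 3 | 21% | 59 |
| 2 | under 0.1% | 131 |

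With ±5, the rule would also declare equality in 31% (n = 21) or 35% (n = 25) of trials when the true gap is 3 units.

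**The case against.** The strongest reply is that the T1 sentence is a background expectation. The Discussion places the main hypothesis at follow-up, none of the stated objectives is equality at T1, and a margin or interval rule for a secondary time point is usually left to an analysis plan that is not shown here. That reply stands as far as it goes. It limits the weight of the point, and the lack of an equivalence margin is not held against the protocol. It does not remove the mismatch, because {20a} does state the sequence of AHA tests and that sequence does not address a hypothesis stated in {7}.

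A reader might infer four stronger things that the documents do not support:

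- **That non-significance will be read as equality.** No section says so. The step to a common time effect is described only as exploration.
- **That a superiority design cannot address equality at all.** The same data can, through a between-arm interval, or through a margin if one is justified.
- **That any non-significant result is compatible with a gap above 5.** At 21 per arm this needs an observed gap of at least 1.57 units. If the arms are truly equal, about 67% (n = 21) or 81% (n = 25) of non-significant results exclude 5.
- **That 5 units is the natural bound for equality.** {14} gives it as the smallest detectable difference and as the effect to be detected, never as an equality margin.

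**Conclusion.** The point holds in limited form. The protocol states a secondary hypothesis of equal AHA gains at T1, and its stated tests do not answer it. Non-significance alone would be weak evidence: the 95% limit can reach 6.9 units with 21 per arm or 6.3 with 25, and a true 3-unit gap would go undetected in more than half of trials. An observed gap near zero would be informative and would exclude 5 units.

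The primary T2 superiority objective and the sample size are unaffected. The figures assume a t-test on change scores with SD 5.5 at T1, and the mixed model's precision may differ. With a ±5 margin, power if the arms are truly equal falls to 58% (n = 21) or 70% (n = 25) at SD 6.5, and rises to 94% or 97% at SD 4.5.

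**What to change.** In Statistical methods {20a}, add that the model-based between-arm difference in T0–T1 AHA change will be reported with its 95% CI, whether or not the interaction is significant.

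In Objectives {7}, word equal improvement at T1 as an expectation, and say that it will not be concluded from a non-significant test or from similar within-arm changes.

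If the sponsor wants to claim equality formally, it should prespecify and justify a margin and require the 90% CI of that difference to lie within it. Five units is the only anchor in the document and is generous, since it equals the effect the trial is sized to detect. A 3-unit margin would be badly underpowered at the planned size.

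The cost is a few sentences, with no extra children or visits. The downside is that an equality claim at T1 becomes harder to make.

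### The predicted AHA divergence during follow-up (T1 to T2) has no between-arm test of its own; after a significant interaction, the only T1–T2 tests named are within each arm

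*Protocol article*

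**What the plan says.** Objectives {7} expects equal gains in the two arms immediately after therapy. For the next six months it states: "we expect further improvements in bimanual performance during the follow-up period for participants who received somatosensory discrimination therapy because of the improved upper limb use", and it expects no such further gain after motor therapy.

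Statistical methods {20a} fixes the order of testing:

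1. The between-arm step: "interactions between therapy and time will be analyzed to test for differences in improvements over time between both groups". It uses all three visits.
2. "When a significant interaction is identified, time trends will be tested in both therapy groups separately (time-effect"). If the interaction is not significant, the main effect of time is explored instead, which is not specific to an arm.
3. "Significant time trends will be further investigated with pairwise post hoc tests to compare individual time points". The pairs listed are T0–T1, T1–T2 and T0–T2. For the AHA model, "the post hoc analysis will be Bonferroni corrected". The size of the Bonferroni family is not stated. Cohen's d is planned for these comparisons.

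The general level is stated as: "Level of significance will be set at 0.05, two-sided". Sample size {14} says "a sample size of at least 21 participants is needed in each group", raised to 25. It rests on a 5-unit between-arm difference in improvement and an SD of change of 5.5 units.

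**The concern.** The hypothesis says that the two arms follow different courses over one interval. Showing this takes a comparison of the arms over that interval, and section {20a} names none. A significant T1–T2 change in one arm and a non-significant one in the other does not show that the arms differ, and a non-significant change in a small arm does not show that nothing changed.

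The interaction does not fill the gap. It has two degrees of freedom and can be significant because of T0–T1 alone.

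The T1–T2 divergence is the protocol's stated reason for expecting better bimanual performance at six months. With the tests named, a real further gain after motor therapy could be taken as absent, or a divergence inferred although both arms gained equally during follow-up.

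**Working it through.** **Reproducing the plan's figure.** Two independent means, d = 0.9, two-sided 0.05, noncentral t: power is 0.792 at 20 per group and 0.812 at 21. The stated 21 per group is reproduced. It covers a between-arm difference of 5 units, not a within-arm change.

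**Inputs for the T1–T2 check**
- n per arm: 21 to 25 (Sample size {14}).
- SD of T1–T2 change: assumed 5.5. The plan gives 5.5 only for changes from baseline. Range shown: 4 to 7.
- True further gain in the motor arm: assumed 2.75 units, which is 2.75/5.5 = 0.5 SD of change. The documents do not give this figure, and it lies below the 5-unit smallest detectable difference.
- Level: 0.05/3 = 0.0167, assuming that the three pairs within one arm form the family.

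**Within-arm T1–T2 test.** Paired t-test with noncentrality (gain/SD) × √n:
- n = 21: 0.5 × √21 = 2.291 against a critical value of 2.613. Power 0.395, miss rate 60.5%.
- n = 25: 0.5 × √25 = 2.500 against 2.574. Power 0.483, miss rate 51.7%.

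| Variation | Miss rate, n = 21 | Miss rate, n = 25 |
|---|---|---|
| Uncorrected 0.05 | 41% | 33% |
| Bonferroni over six pairs (both arms) | 71% | 63% |
| Pooled model error, three pairs | 57% | 49% |
| SD 4, three pairs | 30% | 20% |
| SD 7, three pairs | 76% | 71% |
| Gain of 5 units, SD 5.5, three pairs | 7% | 3% |

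**Effect of the interaction gate.** The planned sequence was simulated: interaction F at 0.05, time F within each arm at 0.05, then a paired T1–T2 test at 0.0167. There were 20,000 runs per scenario. The SD of change was 5.5 for every pair of visits, with equal correlations.
- *No difference between arms at any visit, both gain 2.75 units over T1–T2.* Exactly one arm is T1–T2-significant in about 4% of trials, and about 2% have the hypothesised direction. Without the gate this would be 2p(1−p): 2 × 0.395 × 0.605 = 48% at n = 21 and 2 × 0.483 × 0.517 = 50% at n = 25.
- *Arms differ by 5 units over T0–T1, then both gain 2.75 units.* Exactly one arm is T1–T2-significant in about 42% (n = 21) to 46% (n = 25) of trials, and about 21–23% have the hypothesised direction. There is no divergence during follow-up in this scenario.
- *Follow-up gains of 7.75 units (somatosensory) and 2.75 units (motor).* The gate passes in about 86–92% of trials. Given that it passes, the motor arm's real gain is non-significant in about 55–66%.

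**Power of the missing contrast.** For a between-arm difference in T1–T2 change of 0.5 SD, noncentrality is 0.5 × √(n/2), which is 1.62 at n = 21 and 1.77 at n = 25. Power at 0.05 is 0.35 and 0.41. For 5 units at SD 5.5 it is 0.82 and 0.88.

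**The case against.** The strongest case on the other side has four parts.

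- *The claim would not rest on one non-significant test.* A significant between-arm interaction, a significant time trend and a significant T1–T2 gain in the somatosensory arm would also be needed. This stands. A reader might infer that a single null result in the motor arm carries the whole hypothesis; the planned sequence does not support that.
- *The gate does real work.* A reader might conclude that equal courses in both arms would produce a one-arm-only pattern about half the time. That holds only if the gate is ignored; with it the figure is about 4%. The higher figure returns only if the arms already differ by about 5 units at T1, which runs against the protocol's own expectation of equal gains by then. This stands as a limit on size. It does not make the interaction a test of T1–T2.
- *The misreading is inferred.* Nowhere does the protocol say that a non-significant T1–T2 test will be reported as no improvement, and it plans effect sizes for the pairwise comparisons. This also stands. However, section {20a} offers no other test for that half of the hypothesis.
- *An extra contrast may belong in an analysis plan that is not shown, and it has low power for small differences.* The first part carries limited weight, because the article itself sets out a test sequence that does not answer a hypothesis it states. The second part is true and is a cost of the fix.

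**Conclusion.** The concern holds as a mismatch between a stated hypothesis and the stated tests. The predicted T1–T2 divergence has no direct test, and the absence of further gain after motor therapy could be supported only by non-significance in 21 to 25 children.

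The size depends on assumptions. The miss rate of 52–61% requires an SD of T1–T2 change of 5.5, a 2.75-unit gain, a paired test and Bonferroni over three pairs. A statement that the test misses such a gain more than half the time therefore does not hold in general. For a gain as large as the smallest detectable difference the problem is small at SD 5.5.

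A reader might also infer that the six-month primary result is undermined. This point does not bear on it, because it concerns only a supporting hypothesis about the course between T1 and T2. It is a minor improvement, worth making because it costs almost nothing.

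**What to change.** Add to section {20a}: the hypothesis of further gain during follow-up is tested by the between-arm difference in T1-to-T2 AHA change, a one-degree-of-freedom contrast from the planned mixed model, reported with its 95% CI. Divergence during follow-up is claimed only from this contrast. Each arm's T1–T2 change is reported as an estimate with its CI, and a non-significant motor-arm test is not read as absence of gain.

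The cost is a sentence or two and one contrast from a model already planned, with no new data. The downside is that the contrast may well be inconclusive for small differences (power 0.35 to 0.41 for 0.5 SD). The CI would show that uncertainty openly.
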